### Primary outcomes

The primary outcomes of the study will be the proportion of participants with a diagnostic status of MDE using the electronic Psychological Assessment Scale (e-PASS) [34] and change in mean self-report depressive symptoms using the shortened version of the depressive subscale from the Depression, Anxiety, and Stress Scale (DASS) [35]. Autobiographical memory specificity will be assessed at all time-points using the standard ten-item Autobiographical Memory Test (AMT), with five positive and five negative cue words [36]. We are primarily interested in the changes in outcome measures between baseline and 3 months.

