### Power calculation

Using G*Power V.3.1 [44], it was calculated that a total sample of 128 participants will be needed. This will be sufficient to detect a moderate-sized, clinically meaningful between-groups effect of *d* = 0.50, with 0.80 power and alpha level of 0.05 (two-tailed), while controlling for amount of usual care treatment (type and amount monitored at each time-point). We will aim to recruit 154 participants at baseline to allow for 20% attrition.

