### Statistical analysis

All assessments will be completed using an online format, with data stored online on a secure server accessible by the researchers only. Data entry is completed by participants online and responses are restricted to a predetermined range. The data analyst will be blinded to the condition of participants. Analyses will be on an intention-to-treat basis (i.e., include all randomised participants that complete two or more time-points in the linear mixed models analysis, regardless of the dose of c-MeST or usual care received), with supplementary per protocol analyses (i.e., analysis of participants that have completed all time-points). Linear mixed models will be conducted to assess differences between conditions on the primary and secondary outcomes at each time-point relative to baseline. This statistical method will facilitate inclusion of participants with missing data using a full-information ML estimator. Condition will be modelled as a fixed effect. Time will be modelled as a random effect, grouped within participants. If the groups differ in how much treatment they received in usual care during their participation in the trial, this will be used as a covariate in analyses.

To test mediation effects, primarily whether the effects of group on depressive symptoms over time is mediated through changes in AMT scores over time, analyses will be conducted using a bias-corrected bootstrap test. Power calculations indicate that the sample size will provide power of 0.80 to detect significant indirect effects given small-to-moderate effect sizes between group and depression change, and small-to-moderate effect sizes between changes in AMT scores and depressive symptoms [45]. Given the small number of sites anticipated to be used for recruitment into the present study, site will be dummy coded and included as a covariate in all analyses to adjust for potential between-site differences in outcomes.

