### Procedure

Eligible help-seeking youth reporting depressive symptoms will be identified by trained mental health workers through normal intake procedures at participating services. Exclusion criteria of psychotic, neurodevelopmental and substance use disorders will also be assessed at this point. The youth will be informed of the study and asked for permission to be followed up by a member of the research team and invited to participate. They will then be sent an online link with a plain language statement to read (Additional file 2). Consent to participate will be given by clicking an arrow to take them to the next page at the end of the plain language statement to advise of this. They will then complete screening questions to verify eligibility. If participants are eligible, they will be randomised to one of the two conditions (c-MeST and usual care *or* wait-list c-MeST (to be offered in 6 months) and usual care) using computer-generated simple randomisation following completion of the baseline questionnaire. The researchers will be blinded to this process. Participants randomised to c-MeST and usual care will have immediate access to the online c-MeST program and complete online questionnaires at baseline, 1-, 3-, and 6-month time-points. All participation will be online and either involve accessing the memory intervention application or accessing surveys which will be completed via Qualtrics. Participants will receive automated prompts to complete survey measures at each time point. During the first month of access to the intervention, participants will be prompted with automated reminders every second day to engage in the modules. Participants randomised to wait-list c-MeST and usual care condition will complete online questionnaires and receive access to the c-MeST program after the 6-month follow-up. Therefore, all participants will have received usual care and c-MeST by the cessation of the study. No adverse or serious harm is anticipated as part of the online intervention; however, participants will be able to access support through their usual care provided and a list of contact details for support services will also be provided to participants.

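### The DASS effect is a difference in change from baseline; adjusting for the baseline score already collected would be more precise at no cost

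*Protocol article*

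**What the plan says.** The Study design section crosses two conditions with four time-points, and baseline is the first of the four. The Primary outcomes section defines the continuous primary outcome as change in the short-form DASS depression score and adds: "We are primarily interested in the changes in outcome measures between baseline and 3 months". The Statistical analysis section specifies: "Linear mixed models will be conducted to assess differences between conditions on the primary and secondary outcomes at each time-point relative to baseline". It names two covariates: site in all analyses, and amount of usual care if the arms differ on it. Neither a baseline score as covariate nor a common baseline mean for the two arms is mentioned.

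Under Procedure, participants are allocated "using computer-generated simple randomisation following completion of the baseline questionnaire". Under Power calculation, "it was calculated that a total sample of 128 participants will be needed", which is described as "sufficient to detect a moderate-sized, clinically meaningful between-groups effect of" d = 0.50 with power 0.80 and two-sided alpha 0.05. The SD on which d is expressed is not stated, nor is any correlation between baseline and follow-up.

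**The concern.** Read literally, the model estimates a mean for each arm at each time-point, and the DASS effect is the arm difference at 3 months minus the arm difference at baseline. With complete data that is a comparison of change scores: the baseline score is subtracted with its coefficient fixed at 1.

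Since baseline precedes randomisation, the true baseline means of the two arms are equal. Estimating their difference and subtracting it adds noise and removes no systematic error. Using the same baseline score as a covariate lets the data set its coefficient, and in large samples this never increases the variance. At stake is precision on a primary outcome and, depending on how d = 0.50 was meant, whether 128 participants deliver the stated power. The point covers DASS, AMT and the secondary scales. It does not cover MDE status.

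**Working it through.** **Inputs from the protocol.** Total 128; d = 0.50; power 0.80; two-sided alpha 0.05. Equal arms of 64 are assumed, because no allocation ratio is given.

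**Assumed inputs, not in the protocol.** The correlation rho between baseline and 3-month DASS, taken as 0.3 to 0.6, and the ratio k of the baseline SD to the 3-month SD, taken as 1 or 0.8. Everyone enters in a current MDE, so a baseline SD below the 3-month SD (k < 1) is plausible.

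**Step 1: reproduce the stated figure.** A two-sample t-test (noncentral t) with 64 per arm and d = 0.50 has power 0.801, so 128 reproduces. A two-group ANCOVA F-test with one covariate that removes no variance also gives 128 and 0.801.

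**Step 2: variances, in units of the 3-month variance.**
- Change score: 1 + k² − 2·rho·k, which is 2(1 − rho) at k = 1.
- Baseline-adjusted: 1 − rho², whatever k is.
- Difference: (1 + k² − 2·rho·k) − (1 − rho²) = (k − rho)², which is never negative.

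Generalised least squares for the four-time-point model with separate arm-by-time means (k = 1, 64 per arm) gave exactly the change-score SE under both compound-symmetry and autoregressive covariance: 0.209, 0.194, 0.177 and 0.158 SD at rho 0.3, 0.4, 0.5 and 0.6. With a common baseline mean the SEs were 0.169, 0.162, 0.153 and 0.141, equal to the ANCOVA values.

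**Step 3: variance ratio, adjusted to change = (1 − rho²)/(1 + k² − 2·rho·k).**

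| rho | k = 1 | k = 0.8 |
|---|---|---|
| 0.3 | 0.91/1.40 = 0.65 | 0.91/1.16 = 0.78 |
| 0.4 | 0.84/1.20 = 0.70 | 0.84/1.00 = 0.84 |
| 0.5 | 0.75/1.00 = 0.75 | 0.75/0.84 = 0.89 |
| 0.6 | 0.64/0.80 = 0.80 | 0.64/0.68 = 0.94 |

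**Step 4: power with 128 analysed, if d = 0.50 is on the raw 3-month SD.** The effective d is 0.50 divided by the square root of the variance in step 2.

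| rho | Change, k = 1 | Change, k = 0.8 | Adjusted |
|---|---|---|---|
| 0.3 | 0.66 | 0.74 | 0.84 |
| 0.4 | 0.73 | 0.80 | 0.87 |
| 0.5 | 0.80 | 0.87 | 0.90 |
| 0.6 | 0.88 | 0.93 | 0.94 |

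The change contrast does worse than a plain comparison of 3-month scores when 1 + k² − 2·rho·k > 1, that is, when rho < k/2. As 128 gives almost exactly 0.80 for the plain comparison, rho < k/2 is also where the change contrast drops below 0.80. At k = 1, the total needed for 0.80 power is 178, 154, 128 and 104 for the change contrast and 118, 108, 98 and 84 with adjustment.

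**Step 5: if d = 0.50 is on the change-score SD.** The change contrast has power 0.80 at 128 for every rho and k. Only the variance ratio in step 3 remains.

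**The case against.** A mixed model with a contrast relative to baseline is common and valid. Three stronger readings are tempting, and the documents support none of them.

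- *The trial will miss 0.80 power.* A reader might infer this, or that 128 contradicts the change contrast. It would require d on the raw-score SD and rho below k/2. The protocol gives neither rho nor k, and since the outcome is defined as change, d on the change-score SD is a natural reading. The range restriction that makes a low rho plausible also makes k < 1 plausible, and that lowers the threshold: at k = 0.8 it is 0.4, not 0.5.
- *Chance baseline imbalance under simple randomisation is a further bias.* Over randomisations the change contrast is unbiased. An imbalance shifts the estimate only conditionally on having occurred, and that noise is already in the change-score variance. Counting it separately would count it twice.
- *A common baseline mean has been ruled out.* It has not. An article condenses its full protocol, and the wording relative to baseline is compatible with such a constraint. If the full plan contains it, the precision is already secured.

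The gain can also be small: at k = 0.8 and rho 0.6, power is 0.93 without adjustment and 0.94 with it.

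What stands is that the article goes beyond silence. It fixes the outcome as change, the contrast as relative to baseline, and the covariates as site and usual care. An analyst following that text would fit the less precise contrast.

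**Conclusion.** The point holds as a free improvement in efficiency, not as an error that invalidates the test. As written, the continuous outcomes are compared by change from baseline. Asymptotically, adjustment is never less precise, and it is strictly more precise unless rho = k. Over the assumed rho of 0.3 to 0.6, the saving in variance is 20 to 35% at k = 1 and 6 to 22% at k = 0.8.

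The power consequence is conditional. With d on the raw 3-month SD, 128 analysed and rho below k/2, the change contrast falls short of 0.80, while the adjusted contrast stays at or above it (0.84 to 0.94 over the range shown). With d on the change-score SD, the stated power stands. The algebra is certain; whether this trial would lose power cannot be settled from the protocol.

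**What to change.** In the Statistical analysis section, for the continuous outcomes, specify one of two models:

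- (a) the 1-, 3- and 6-month scores as outcomes, with the baseline score and its interaction with time as covariates; or
- (b) baseline kept as a modelled time-point, with both arms constrained to one common baseline mean.

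Report the adjusted between-arm difference at 3 months as the DASS effect. The two forms give nearly the same result with complete data but can differ when follow-up is missing, so one should be named in advance. Either can keep the existing rule that participants need at least two completed time-points. Form (b) could also take in participants with a baseline score only, but that would change the stated analysis set and is not needed here.

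In the Power calculation section, state which SD d = 0.50 refers to. If it is the raw-score SD, add that 128 analysed participants give at least 0.80 power for the baseline-adjusted comparison.

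The cost is a few sentences, with no new data and no more participants. The change should be settled before the analyst sees outcomes by arm.

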## Methods/design

### Study design

We will conduct an online, randomized controlled trial using a two (condition: usual care and c-MeST, usual care only control group) × four (time-point: baseline, 1, 3 and 6 months post-intervention) factorial design. The usual care control group will complete questionnaires and be offered access to c-MeST at the end of the study. c-MeST has demonstrated efficacy in improving specificity in an online format and therefore this trial will determine whether c-MeST as an adjunct to treatment as usual is superior to treatment as usual only. See Fig. 1 for schedule of enrolment, intervention and assessment. A Standard Protocol Items: Recommendations for Interventional Trials (SPIRIT) 2013 checklist is provided as Additional file 1.

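### The mixed-model description makes time random only and names no condition-by-time term, which conflicts with the 3-month change from baseline that the protocol sets out to compare

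*Protocol article*

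**What the plan says.** All the relevant text is in the Methods/design part of the protocol article.

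- **Model terms (Statistical analysis).** "Condition will be modelled as a fixed effect", and then "Time will be modelled as a random effect, grouped within participants".
- **Covariates (Statistical analysis).** "site will be dummy coded and included as a covariate in all analyses". If the arms turn out to differ in the amount of usual care received, "this will be used as a covariate in analyses".
- **Purpose of the model (Statistical analysis).** The linear mixed models are to "assess differences between conditions on the primary and secondary outcomes at each time-point relative to baseline".
- **Main contrast (Primary outcomes).** "We are primarily interested in the changes in outcome measures between baseline and 3 months".
- **Design (Study design).** Two conditions crossed with "four (time-point: baseline, 1, 3 and 6 months post-intervention) factorial design".
- **Power (Power calculation).** 128 participants for a between-group effect of d = 0.50 "with 0.80 power and alpha level of 0.05 (two-tailed").

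**The concern.** A difference between arms at a given visit, relative to baseline, is a condition-by-time contrast in the means. It needs time in the fixed part of the model and an interaction of time with condition. The two sentences that assign terms give time a random role only and name no interaction. Site and usual care are further fixed terms, but neither supplies a time contrast.

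The four visits are planned, and their mean differences are the research question. A random effect of time describes how participants vary around a mean course. It can be added to fixed time effects but does not replace them.

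At stake is what the treatment estimate means for the DASS depression score and the continuous secondary outcomes. The literal model returns one coefficient that mixes the pre-treatment wave with the follow-up waves. An analyst following the purpose sentence and one following the model sentences would report different quantities, and each could cite the protocol. That choice should not remain open once results are known.

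**Working it through.** **1. The plan's own figure.** A two-sample t-test with d = 0.50, two-sided alpha 0.05 and power 0.80 needs 63.77 per arm, rounded up to 64. That gives 128 in total with power 0.801, so the stated number reproduces (1:1 allocation assumed). This point does not change it.

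**2. Terms in each model.** Before the covariates:

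- Literal model (condition fixed; random intercept and time slope by participant): fixed effects are the intercept and condition. No parameter is the 3-month change.
- Condition × categorical time, same random part: intercept, three time terms, condition, and three interactions (1, 3 and 6 months against baseline). The 3-month interaction is the contrast named in Primary outcomes.

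**3. What the literal coefficient estimates.** With complete data and equally weighted waves (the random-intercept case), its expectation is (0 + d1 + d3 + d6)/4. The zero is the baseline wave, where randomisation makes the expected difference nil. This shrinkage does not depend on the within-person correlation r.

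**4. Size.** The documents give no r, time trend or effect course. Assumed: r = 0.5 at all lags (compound symmetry), SD 1, 64 complete per arm, normal approximation, power = Φ(effect/SE − 1.96).

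Literal coefficient: variance of a four-wave mean = (1 + 3 × 0.5)/4 = 0.625; SE = √(2 × 0.625/64) = 0.140.

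| Assumed effect at 1 / 3 / 6 months | Expected coefficient | Power |
|---|---|---|
| 0.5 / 0.5 / 0.5 | 1.5/4 = 0.375 | about 0.76 |
| 0.2 / 0.5 / 0.5 | 1.2/4 = 0.30 | about 0.57 |
| 0.1 / 0.5 / 0.3 | 0.9/4 = 0.225 | about 0.36 |

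The 3-month effect is 0.50 in every row. Estimated directly:

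- Condition × time at 3 months: variance of change = 2(1 − 0.5) = 1; SE = √(2/64) = 0.177; power about 0.81.
- The same with baseline adjustment: variance = 1 − 0.5² = 0.75; SE = √(1.5/64) = 0.153; power about 0.90.

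**5. Range over r.** For the sustained effect, using the same formulas:

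| r | SE, literal | Power, literal (0.375) | SE, 3-month contrast | Power, 3-month contrast (0.50) |
|---|---|---|---|---|
| 0.3 | √(2 × 0.475/64) = 0.122 | about 0.87 | √(2 × 1.4/64) = 0.209 | about 0.67 |
| 0.5 | 0.140 | about 0.76 | 0.177 | about 0.81 |
| 0.7 | √(2 × 0.775/64) = 0.156 | about 0.67 | √(2 × 0.6/64) = 0.137 | about 0.95 |

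So the direction of the power difference depends on r. The attenuation and the change of target do not.

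**6. Chance baseline imbalance.** Suppose the arms differ by D at baseline, there is no treatment effect, and r = 0.5. The later waves are then expected to differ by 0.5D, and the literal coefficient by (D + 3 × 0.5D)/4 = 0.625D. For D = 0.30 that is about 0.19. The unadjusted 3-month change moves the other way, by (0.5 − 1)D = −0.15. Baseline adjustment removes the shift.

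**7. Simulation check (illustrative, few runs, assumed variances and trend).** With random time slopes, 64 per arm and a true 3-month effect of −0.50 (30 runs), the literal coefficient averaged −0.42 and the 3-month interaction −0.51. With an imposed, persistent arm difference of −0.30 and no difference in change (20 runs), the literal coefficient averaged −0.37 and was significant in 75% of runs. The 3-month interaction averaged −0.06 and was significant in 5%. That fixed shift is a stress test; randomisation would not produce it on average.

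**The case against.** The strongest reply is that two short sentences in a condensed article are not a full model formula. The purpose sentence in the same section names a condition-by-time contrast, Study design crosses condition with time-point, and nothing says an interaction will be left out. The sentence on time may be loose wording for repeated measures within participants, or for random slopes. Much of this stands. A reader might infer that condition is the only fixed effect; the site and usual-care covariates contradict that. A reader might also infer that the trial cannot estimate the 3-month change. The documents do not support that either: it is true only of the model read literally, and an analyst keeping to the purpose sentence would have to fit the interaction.

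It is also fair to say that the power figures rest on assumed correlations and effect courses. The gap is small for a sustained effect at r = 0.5 and reverses at r = 0.3. The equal-weight formula need not hold exactly under random slopes.

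What does not stand is the plea of condensation. The article does not leave the role of time to another document. It assigns time a role, and that role does not fit the contrast promised in the same section.

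Baseline adjustment belongs in a different class. An unadjusted change-from-baseline contrast in a mixed model is valid, so its absence is no error.

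**Conclusion.** The concern holds as a conflict between the stated model and the stated contrast. The model sentences omit the fixed time and condition-by-time terms that the protocol's own aim requires.

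Read literally, the treatment coefficient is a time-averaged difference that includes baseline. With equally weighted waves, a sustained 0.50 SD effect appears as 0.375, and as 0.30 or 0.225 under the two later-emerging courses. Under r = 0.5, compound symmetry and 64 complete per arm, power is about 0.76, 0.57 and 0.36, against about 0.81 for the 3-month contrast. The power comparison depends on these assumptions. The firm conclusion is that the literal coefficient answers a different question and is open to chance differences at baseline. It remains uncertain which model the trial will fit, since the surrounding text points to an interaction.

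**What to change.** For the continuous outcomes, replace the sentences on condition and time with a full statement of the model:

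- fixed effects: time as a categorical factor, condition × time, and site (with usual care handled as the protocol decides);
- within-person structure: a participant random intercept, or an unstructured covariance over the four visits;
- primary contrast: the condition difference at 3 months, with the 1- and 6-month contrasts taken from the same model.

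As an optional gain in precision, constrain the baseline means to be equal across arms or adjust for the baseline score. Under the r = 0.5 assumptions this lowers the SE from about 0.177 to 0.153 and raises power from about 0.81 to 0.90.

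The cost is a wording change, to be made and dated before the analyst sees outcomes by arm. Data collection, software and the sample size of 128 are unaffected.

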### Participants

The inclusion criteria will be: (i) 15–25 years, (ii) recent or current engagement with a mental health service provider (iii) residing in Australia, (iv) a current diagnosis of an MDE and (v) internet access. The exclusion criteria will be: (i) non-fluency in English and (ii) psychotic, neurodevelopmental and substance use disorders.

Regarding risk, if a participant scores ≥ 21 on the Suicidal Ideation Attributes Scale (the cutoff for risk of suicidal behaviour) then they will receive information regarding helplines/support they might wish to contact. Otherwise, duty of care for risk will be managed by usual risk management protocols through the service they are receiving to increase the generalisability of the findings, comorbid mental health disorders will not be an exclusion criterion of those listed above.

Usual care for participants will vary. As we are recruiting participants at the time of engagement with a mental health service they will be receiving evidence-based treatment for their depressive symptoms (such as anti-depressant medication or psychological/counselling support). Participants will be free to cease involvement in the study at any time.

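### The treatment comparison is adjusted for usual care received after randomisation if the arms differ on it, which can move the estimate off the intention-to-treat effect in either direction

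*Protocol article*

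**What the plan says.** The protocol article, Statistical analysis, gives the rule in one sentence: "If the groups differ in how much treatment they received in usual care during their participation in the trial", then "this will be used as a covariate in analyses". Nothing confines it to a sensitivity analysis or exempts the primary outcomes.

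Four other places bear on it:

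- **Procedure.** Participants are allocated "using computer-generated simple randomisation following completion of the baseline questionnaire". Care received while taking part is therefore care received after allocation.
- **Participants.** Usual care is active treatment for the outcome: "they will be receiving evidence-based treatment for their depressive symptoms".
- **Statistical analysis, intention-to-treat definition.** Randomised participants with at least two time-points are analysed "regardless of the dose of c-MeST or usual care received".
- **Power calculation.** The sample size is said to detect the target effect "while controlling for amount of usual care treatment (type and amount monitored at each time-point"). Here the control for care carries no condition.

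The question the trial sets itself is in Study design: "this trial will determine whether c-MeST as an adjunct to treatment as usual is superior to treatment as usual only".

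**The concern.** That question asks for the total effect of being allocated c-MeST on top of whatever usual care follows. Care after allocation may be part of that effect: a participant who improves may use less care, and one who becomes more engaged may use more. It may also act on symptoms directly, because it is treatment, and it may track underlying severity.

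Conditioning on such a variable does two things. It takes out whatever part of the c-MeST effect runs through care. It also opens a path through severity that randomisation had closed. Either way the coefficient for condition no longer answers the Study design question.

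The trigger does not help. A chance imbalance in on-trial care causes no average bias that needs correcting, whereas a real difference in care caused by allocation is where adjustment does harm, and where the rule is most likely to fire.

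The text is also inconsistent with itself. It analyses people whatever dose of usual care they received, then adjusts for that dose. It also treats the control as unconditional in one section and conditional in another. At stake are the size of the primary estimate and its error rates.

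**Working it through.** **1. The plan's own figure.** Inputs from Power calculation: d = 0.50, two-sided alpha 0.05, power 0.80, total 128. Equal arms are assumed, since the ratio is not stated. Two-sample t-test, noncentrality d × √(n/2) = 0.50 × √32 = 2.83 with 126 degrees of freedom: power is 0.8015 at 64 per arm and 0.795 at 63. Spending one degree of freedom on a covariate gives 0.8014. So 128 is reproduced, and whether the covariate is always or conditionally included does not change it.

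**2. Formula for the adjusted effect.** With outcome and care use both scaled to SD 1:

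adjusted effect = total effect − (partial slope of symptoms on care) × (effect of c-MeST on care).

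The article gives neither of the last two quantities, so both are assumptions. The slope can take either sign. If care lowers symptoms by b per SD, and care and symptoms share a severity factor with loading g on each, the slope is g² − b.

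**3. Central illustration.** Total effect -0.50; c-MeST lowers care by 0.4 SD.

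- Slope +0.25 (care mainly marks severity): -0.50 − (0.25 × -0.4) = -0.40.
- Slope -0.25 (care mainly relieves symptoms): -0.50 − (-0.25 × -0.4) = -0.60.

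Those are the values if the covariate always enters. The stated rule enters it only if the arms differ. Taking a difference to mean p < 0.05, the chance of firing with a 0.4 SD shift at 64 per arm is the t-test power at d = 0.40, which is 0.61.

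Simple weighting for the positive slope gives 0.61 × (-0.40) + 0.39 × (-0.50) = -0.44. Simulation gives about -0.42, because the trials that fire are those with a larger than average observed care difference, and hence a larger correction.

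| Analysis (true effect -0.50, care lowered 0.4 SD) | Slope +0.25 | Slope -0.25 |
|---|---|---|
| Unadjusted | -0.50, power 0.80 | -0.50, power 0.80 |
| Stated conditional rule | -0.42, power 0.66 | -0.58, power 0.90 |
| Always adjusted | -0.40, power 0.62 | -0.60, power 0.92 |

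With a true total effect of zero and the same shift, the conditional rule has type I error of about 0.07, against 0.05 unadjusted.

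**4. Range.** Conditional rule, 128 participants, true effect -0.50, care shift 0.3 to 0.5 SD, trigger firing in about 38% to 81% of trials:

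| How care relates to symptoms | c-MeST lowers care | c-MeST raises care |
|---|---|---|
| Relieves symptoms only (b = 0.2 to 0.3, g = 0) | -0.54 to -0.64 | -0.46 to -0.36 |
| Marks severity only (b = 0, g = 0.5) | -0.46 to -0.39 | -0.54 to -0.61 |
| Both, nearly cancelling (b = 0.2, g = 0.5; slope 0.25 − 0.20 = 0.05) | -0.49 to -0.48 | -0.51 to -0.52 |

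Power runs from 0.53 to 0.95 across these cases. Under a null total effect with a 0.5 SD shift, type I error is 0.08 to 0.12 in the first two rows and about 0.05 in the third.

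**5. No effect of c-MeST on care.** The rule fires in about 5% of trials, the mean estimate is -0.50 and type I error is about 0.05. The unadjusted analysis was unbiased in every scenario.

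**The case against.** Several points on the other side are sound.

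- **Nothing in the article shows that c-MeST changes care use.** It is an automated, low-intensity add-on, and usual care is delivered by separate services. If it leaves care use alone, the rule is harmless. This stands: every figure for bias is conditional on an assumption.
- **A reader might infer that the rule shrinks the c-MeST effect and leaves the trial underpowered.** The documents do not support a direction. Describing usual care as effective treatment makes a negative slope at least as defensible as a positive one, and with reduced care use that inflates the estimate. An effect of -0.40 with power of about 0.6 also belongs to unconditional adjustment, not to the conditional rule.
- **A reader might infer that adjustment happens exactly when c-MeST has changed care.** It does not: a real 0.4 SD shift is missed about 39% of the time, and chance fires the rule about 5% of the time.
- **The rule is stated in advance, depends on care rather than outcome, and the analyst is blinded to condition.** This stands, so it should not be called outcome-driven model selection. A fuller analysis plan may define what counts as a difference, and its absence from an article is no fault.
- **Adjusting separates c-MeST from unequal co-treatment.** That is a different quantity, an effect with care held fixed. It requires no unmeasured common cause of care and symptoms, which is hard to believe when severity drives care, and it is not the Study design question.

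The mismatch between the two sections has almost no numerical consequence (0.8015 against 0.8014). It is a wording conflict, and neither version rescues the plan, because both include care recorded after randomisation.

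**Conclusion.** The point holds. The article itself fixes a rule under which the primary comparison may be adjusted for a variable measured after randomisation that allocation could affect, and this sits badly with its own intention-to-treat wording. If c-MeST changes care use and care use is related to depression, as a treatment or as a marker of severity, the estimate stops being the intention-to-treat effect of adding c-MeST.

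The sign of the bias cannot be known in advance. In the central illustration it is about 0.08 SD either way on a true effect of 0.50, with type I error of about 0.07 under the null. It is near zero if the pathways cancel, and zero if care use is unaffected. These figures rest on an assumed 0.4 SD shift in care, partial slopes of ±0.25, equal arms, a 5% trigger and a continuous outcome at a single follow-up. MDE status, the other primary outcome, was not quantified.

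The case for changing the rule does not depend on those values: the unadjusted comparison needs none of these assumptions.

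**What to change.** In Statistical analysis, delete the conditional rule and state that the primary analysis does not adjust for care received after randomisation. If care is wanted as a covariate, use only the type and amount recorded at baseline, named in advance and included whatever the observed balance. Report on-trial care by arm, and label any analysis adjusted for it exploratory. In Power calculation, reword the phrase on controlling for usual care so that it refers to baseline care only, or remove it.

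The cost is two sentences of wording. No new data are needed, because care is already monitored at each time-point, of which baseline is one. The sample size of 128 is unchanged: 64 per arm without the covariate still gives power of 0.80.
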